## Abstract

**Background:**

Prostate cancer (PCa) is the most common non-cutaneous malignancy in men and leads to the second most common cause of cancer related mortality in men. Early detection of PCa allows for a potentially curative intervention. Most men will live over a decade from the time of their PCa diagnosis. Thus, treatments must balance curative interventions with their impact on quality of life. Radical prostatectomy (RP) is one such potentially curative intervention but often leads to erectile dysfunction (ED) and urinary incontinence (UI). Approximately 90,000 RPs are performed each year in the USA. Post-operative ED and UI is thought to occur in part from traumatic peripheral nerve injury (TPNI) to the neurovascular bundles that surround the prostate. Thus, patients undergoing RP may be a population that would benefit from clinical studies that look at TPNI.

**Methods:**

The study is a single-institution, double-blinded placebo-controlled, randomized clinical trial in which patients immediately post-RP receive either 4-aminopyrdine (4AP) or placebo in a 1:1 fashion. The primary outcome is evaluation of the efficacy of 4AP in accelerating the early return of baseline erectile and urinary function post-radical prostatectomy.

**Discussion:**

This study is critical as it could reduce the morbidity associated with RP, a commonly performed operation, and identify a patient population that may greatly benefit into further TPNI research.

**Trial registration:**

ClinicalTrials.gov NCT03701581. Prospectively registered on October 10, 2018.

## Administrative information

Note: The numbers in curly brackets in this protocol refer to the SPIRIT checklist item numbers. The order of the items has been modified to group similar items (see http://www.equator-network.org/reporting-guidelines/spirit-2013-statement-defining-standard-protocol-items-for-clinical-trials/).

## Introduction

### Background and rationale {6a}

Prostate cancer (PCa) is the most common non-cutaneous cancer in men and the second most common cancer to cause death in men (after lung cancer) worldwide, counting 268,490 new cases and causing 34,500 deaths in the USA alone in 2022. Importantly, most men will live for 10 years or more after a diagnosis of PCa. Most PCa is localized at the time of detection, for which there are several options. For clinically localized disease in healthy men, most are left choosing between radical prostatectomy (RP) and radiation therapy (RT). From an oncologic perspective, surgery and radiation have equivalent outcomes. With similar oncologic outcomes between treatment modalities and long survival from diagnosis, patients are left balancing the risks and benefits of each treatment approach. Despite RP being proven to decrease PCa-specific mortality and progression to metastatic disease, RP is still associated with significant quality of life issues, including worsening of erectile function and urinary continence [1]. RP offers whole-gland pathology analysis with lymph node dissection to give more complete staging and an easier ability to interpret Prostate Specific Antigen (PSA) values in the post-operative setting. However, most men will experience iatrogenic urinary incontinence (UI) and erectile dysfunction (ED) post-operatively that may improve over time [2]. This discussion also underscores the need for improvement in our current treatments for localized PCa.

The technique for RP has been refined over the last two decades and has significantly improved the outcomes. Nerve-sparing RP (NSRP) has been shown to reduce the extent of ED and UI post-operatively. NSRP is performed by dissecting the neurovascular bundles off the posterolateral aspect of the prostate on each side. Occasionally, the nerves cannot be spared due to oncologic concerns or if significant inflammation is present. Even when NSRP is performed, approximately 30–60% of men have postoperative ED 1-year after surgery [3, 4]. UI post-RP is complex, and its causes can be multifactorial; however, a component may be the result of mechanical injury to the urinary sphincter from surgical trauma and/or to the peripheral nerves juxtaposed with the prostate that innervate the external urinary sphincter.

Despite all efforts made during a NSRP, much of the ED and UI experienced is still due to traumatic peripheral nerve injuries (TPNI) [5]. TPNI occurs from traction, thermal, or crush trauma. This affects nerves as well as the distal organ and sensory function. A deeper understanding of TPNI emerged only recently. The degree of nerve damage after NSRP is unknown as there are no intraoperative or post-operative clinical tools to evaluate the extent of nerve damage. Clinically, ED and UI can be measured before and after surgery with validated scales such as the simplified International Index of Erectile Function (IIEF-5) and the Michigan Incontinence Symptom Index (M-ISI) instruments, respectively.

Given this background, RP patients offer a reasonable clinical venue to test for the capacity to respond to TPNI treatment as compared to untreated controls. A key target of inquiry is the loss of erectile function, or potency, and urinary continence which are known to be significantly related to neurovascular injury sustained during RP. Currently, recovery of potency and continence in these patients is inconsistent, unpredictable, and often delayed up to 12 months.

Experiments performed using long-standing standard animal models of acute TPNI reveal novel abilities of 4-aminopyridine (4AP) to enhance both the speed and extent of neurologic recovery. 4AP has been employed in the clinic since the early 1980s as a means of providing symptomatic relief in chronic neurodegenerative disorders including multiple sclerosis, myasthenia gravis, and chronic sequelae of spinal cord injury [6–9]. The major mechanism of action is by inhibiting voltage-activated potassium channels. Those undergoing NSRP offer a unique opportunity to test the viability of 4AP to promote accelerated clinical recovery after TPNI. After TPNI, nerve recovery can occur weeks to years after injury. Clinically, patients begin regaining erectile function and continence as well weeks to years after surgery. Given these factors, we chose a 2-month time course of treatment as this is when the steepest recovery curves occur, thus the best time to evaluate if 4AP is helpful in functional recovery after NSRP.

4AP is currently the mainline treatment in the setting of multiple sclerosis [6, 10] and is used in some of the most fragile of neurologically ailing patients. Multiple sclerosis is a demyelinating disorder that affects the peripheral and central nervous systems. The axonal myelin covering is essential for normal nerve impulse conduction. Crush injuries to nerves can damage myelin sheaths while leaving nerve axons intact. This has led to the idea to study the treatment of peripheral nerve traumatic injuries in humans using 4AP.

The published findings relevant to this proposal are as follows:4AP administration in a single dose given directly after TPNI leads to a significant reduction in the dysfunction caused by a sciatic nerve crush injury.Daily treatment with 4AP over several weeks leads to accelerated durable recovery over untreated controls. This recovery is maintained after the dose is cleared from the animal and is associated with structural improvements in the injured nerve (enhanced repair of damaged myelin and an increase in the number of nerve fibers (i.e., axons) at the crush site). This finding in particular stands in contradistinction to the effects seen using 4AP for chronic indications, where symptomatic relief is completely dependent on circulating 4AP and cessation of treatment is associated with loss of symptomatic functional benefit.These effects were replicated with a locally implantable form of 4AP, developed in the laboratory, which may allow for targeted dosing in the future.

### Dosing considerations

The routine use of extended-release 4AP at the proposed dose (10 mg BID) is considered safe in humans, and routine testing for the circulating level of 4AP is not typically undertaken. Reference ranges for dose selection are based on clinical experience and the literature from studies establishing the utility of 4AP for other conditions [11]. 4AP has been studied in humans since the early 1980s, and principles of safe usage are well-established [12, 13].

This trial will employ the currently approved slow-release formulation of 4AP to treat erectile dysfunction and incontinence after RRP.

### Objectives {7}

The purpose of this study is to evaluate the role of 4-aminopyridine (4AP) on the course of recovery after peripheral nerve injury specific to that suffered in the setting of RP surgery. The investigational treatment will be used to test the hypothesis that 4AP speeds the often slow and unpredictable recovery after RP.

### Trial design {8}

This is a single-center double-blind, randomized, placebo-controlled, superiority-designed clinical trial to determine if the use of 4AP can accelerate the return of erectile function to baseline levels. The treatment group will receive the active study drug after surgery for 2 months (60 days), and the placebo group will receive a matching placebo after surgery for 2 months (60 days).

## Methods: participants, interventions, and outcomes

### Study setting {9}

This study is conducted in an academic health center. It was approved by the United States Food and Drug Administration. It was approved by the Institutional Review Board at the University of Rochester Medical Center. All patients are obtained from the University of Rochester Medical Center.

### Eligibility criteria {10}

The following are the inclusion criteria:Male patients with organ-confined, non-metastatic prostate cancer (stages cT1c–T2c) diagnosed in the last 3 months, planning to undergo robotic-assisted laparoscopic bilateral nerve-sparing radical prostatectomy (NSRP)Prostate-specific antigen (PSA) levels less than 15 ng/ml within the last 12 months, with biopsy-proven prostate cancer, for whom postoperative adjuvant therapy (e.g., radiation or androgen deprivation therapy) is not expected to be neededAges 45–75An Abridged International Index of Erectile Function-Erectile Function (IIEF-5) score of greater than or equal to 17 at the time of screeningHas experienced at least 6 months of regular sexual activity and sexual activity during the 12 weeks prior to prostate biopsy or surgeryWillingness to abstain from treatments for erectile dysfunction until 3 months after surgeryWillingness to participate and able to provide informed consent

The following are the exclusion criteria:Planned adjuvant therapy after NSRP based on specimen pathology and patient preference within the first 6 months from surgeryNeo-adjuvant therapy prior to NSRPHistory of recurrent prostate cancerHistory of seizures, multiple sclerosis, stroke, or any other diagnosed neurological disorderHistory of non-organ confined or metastatic prostate cancer (clinical stages T3 or greater)History of known hypersensitivity to 4APPatients with a history of penile surgery other than circumcision or endoscopic urethral stricture surgeryRenal impairment based on calculated GFR (GFR < 60 mL/min)Use of any other aminopyridine medications for any other indication

### Who will take informed consent? {26a}

Urologists will introduce and discuss the nature of the study and answer any questions the patient may have during an in-person pre-operative visit. To minimize the opportunity for any perceived coercion by the subject’s surgeon, patients expressing interest will be referred to the study coordinator to further the study discussion and obtain informed consent. The study coordinator will obtain informed consent prior to the subject’s surgery.

### Additional consent provisions for collection and use of participant data and biological specimens {26b}

Not applicable. There are no additional consent provisions for this study.

### Interventions

#### Explanation for the choice of comparators {6b}

Our treatment comparator is a placebo because there is no current effective therapy for reversing the effects of nerve injury after NSRP. While PDE5 inhibitors have been beneficial in helping men achieve erections after NSRP, studies have not shown that PDE5 inhibitors improve organic erectile function in men who take PDE5 inhibitors versus those who have not after prostatectomy. Furthermore, we standardize the use of PDE5 inhibitors during the first 3 months after surgery because varied use of PDE5 inhibitors between the groups may create a confounding variable that would be difficult to sort out with a study of this size.

#### Intervention description {11a}

Subjects will be randomized equally into one of two groups. Both the subject and investigators will be blinded to group assignment.The treatment group (40 subjects) will receive the study drug daily, in two oral doses, taken at least 12 h apart (approximately 8:00 am; 8:00 pm), starting on the day after surgery with the approximately 8:00 am dose. The treatment group will continue at this same dose and daily dosing regimen for 2 months (60 days).The placebo group (40 subjects) will receive a placebo daily, in two oral doses, taken at least 12 h apart (approximately 8:00 am; 8:00 pm), starting on the day after surgery with the approximately 8:00 am dose. The placebo group will continue at this same dose and daily dosing regimen for 2 months (60 days).

The following are the dosing instructions:Dosing schedule = 1 capsule in the morning and another capsule 12 h later (approximately 8:00 am; 8:00 pm).Dosing to begin the day after surgery with the 8:00 am dose.Subjects will not take more than two capsules in a 24-h period.Subjects will take the capsules whole. They will not break, crush, chew, or dissolve capsules before swallowing. The subjects will be told that the medication is released slowly over time, and if the tablet is broken, the medicine may be released too fast which can raise the chance of having a seizure.The study drug can be taken with or without food.If a dose is missed, they should not make up the missed dose; however, subjects may take the dose within 1 h of the scheduled time. They will be told not to take two doses at the same time but to take the next dose at the regular scheduled time.If the subject is unable to take the study medication due to surgical complications (such as ileus), the doses will be skipped and the subject will resume the study medication once able to take other medications by mouth. The subject will not make up the missed doses.Subjects will be reminded not to take the study drug together with other aminopyridine medications, including compounded 4AP (sometimes called 4-aminopyridine or fampridine).

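### Once the 1-hour late-dose permission is used, returning to the regular clock time gives an 11-hour gap against the stated 12-hour minimum

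*Protocol article*

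**What the plan says.** All the relevant statements are in the protocol article, section Intervention description {11a}, and they apply to both arms.

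- **Minimum spacing.** Capsules are taken daily "in two oral doses, taken at least 12 h apart (approximately 8:00 am; 8:00 pm").
- **Nominal schedule.** The dosing instructions repeat this as "1 capsule in the morning and another capsule 12 h later (approximately 8:00 am; 8:00 pm").
- **Cap.** "Subjects will not take more than two capsules in a 24-h period".
- **Late-dose permission.** A missed dose is not to be made up, but "subjects may take the dose within 1 h of the scheduled time".
- **Next dose.** The sentence after the permission reads: "They will be told not to take two doses at the same time but to take the next dose at the regular scheduled time".

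The section does not say whether the 1 hour covers early as well as late doses. It does not say whether the next dose moves to preserve 12 hours after a late one, or whether the 24-hour period is rolling or a calendar day.

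**The concern.** Two doses a day at fixed times 12 hours apart use up the whole of a 12-hour minimum. Any lateness that is not carried forward to the next dose therefore shortens the following interval below the minimum. The section permits lateness of up to 1 hour and then tells the subject to go back to the clock time. A man who does both has followed two instructions and broken a third.

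After discharge these instructions are followed largely unsupervised for 60 days, and an hour's delay is an ordinary event. Under Post-op day 1, the dosing instructions and the diary are reviewed at every follow-up contact, so study staff need one consistent answer to give. What is at stake is the clarity of an operative instruction. The trial's power and its estimates are not affected.

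**Working it through.** **Inputs**, all from Intervention description {11a}: nominal times 8 am and 8 pm; minimum gap 12 h; permitted deviation 1 h; next dose at the regular time; cap of two capsules per 24-h period; 60 days of two capsules.

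**Notation.** Let dose *i* be taken at 12*i* + *o_i* hours, where *o_i* is its offset from schedule. Then:

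- gap between consecutive doses = 12 + *o_(i+1)* − *o_i*
- span of three consecutive capsules = 24 + *o_(i+2)* − *o_i*

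**Step 1: the plan's own schedule.** With all offsets 0, each gap is 12 h and three consecutive capsules span 24 h. This reproduces the stated 12-h spacing and shows that the schedule has no slack.

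**Step 2: one permitted late dose, then the regular time.** Set *o_i* = 1 and *o_(i+1)* = 0. The gap is 12 + 0 − 1 = 11 h.

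- 9 am to 8 pm the same day: 20 − 9 = 11 h.
- 9 pm to 8 am the next day: 32 − 21 = 11 h.

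A shorter delay of *x* hours gives a gap of 12 − *x*, so any delay that is not carried forward breaches the minimum. One hour is the largest delay permitted. The same-day example is the cleaner one, because it holds even if the 12-h rule is read as spacing only the two doses of one day.

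**Step 3: can the subject avoid the conflict after a late dose?** After a 9 am dose he can take the next at 9 pm. That keeps 12 h and is within 1 h of schedule, but it is not the regular time. Or he can take it at 8 pm, which is the regular time but leaves 11 h. No choice for that next dose meets both instructions.

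**Step 4: the cap.** With *o_i* = 1 and the next two doses on time, the span is 24 + 0 − 1 = 23 h: 9 am, 8 pm, then 8 am. On a rolling window that is three capsules within 24 h. On a calendar-day reading, each day still holds two capsules and the cap is met.

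**Step 5: enumeration.** All sequences of five consecutive doses were checked under three sets of offsets.

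| Offsets allowed | Shortest gap | Shortest span of three capsules |
|---|---|---|
| None (exact) | 12 h | 24 h |
| 0 to 1 h late | 11 h | 23 h |
| 1 h early to 1 h late | 10 h | 22 h |

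The last row applies only if the 1 hour also covers early doses.

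**Step 6: how often it could arise.** There are 60 × 2 = 120 capsules and so 119 intervals. With late doses only, a full 11-h gap needs a dose 1 h late followed by one on time. The interval after that starts from an on-time dose and cannot be below 12 h. Full 11-h gaps therefore cannot be adjacent, and at most 60 of the 119 intervals could be 11 h. This is an upper bound, not an expected count.

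**The case against.** The strongest reply is that the rules can be followed. Exact 8 am and 8 pm dosing meets every one of them. The 1-hour allowance is a permission, so a late dose may be skipped instead. Spacing, permission and cap can also be met together by staying late, for example 9 pm and then 9 am. This stands, and it rules out a reading that a reader might infer: that the dosing rules can never all be met. The conflict arises only when the permission is used, and it is the next-dose sentence that creates it.

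Two further defences do not remove the conflict.

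- **The clock times are approximate.** That wording loosens the times, not the minimum interval. It might stretch the regular time to include 9 o'clock, but nothing tells the subject to carry a delay forward, and the next-dose sentence points him the other way.
- **The next-dose sentence covers only skipped doses.** It follows the late-dose permission directly and is not limited in that way.

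Several stronger readings are tempting, but the article does not support them.

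- **A 10-hour gap or three capsules in 22 hours.** Both need early dosing. The permission stands in the missed-dose sentence, where late-only is the natural meaning.
- **A definite breach of the cap.** This needs a rolling window, which the article does not specify.
- **A seizure risk from an 11-hour interval.** The seizure warning in this section concerns broken capsules releasing drug too fast. No risk is stated for a shorter interval.
- **Misclassified compliance affecting results.** Strategies to improve adherence to interventions {11c} describes a diary and the return of unused medication, with no class based on dose intervals. The analysis is by intention to treat.

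**Conclusion.** The point holds in a narrow form. Within Intervention description {11a}, the 12-hour minimum, the 1-hour permission and the return to the regular time cannot all be met once a permitted late dose has been taken. The shortfall is at most 1 hour, an 11-hour gap against 12.

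This assumes that the permission covers late doses only and that the next-dose sentence applies after a late dose as well as after a skipped one. Three capsules in 23 hours is a further breach only on a rolling reading of the 24-hour period.

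The point is minor. It does not touch the sample size, the endpoint or the analysis, and it is no evidence of harm. It is still worth correcting, because a subject who obeys the late-dose and next-dose instructions breaks the plan's own stated minimum. It is also not a matter of detail left to a fuller document, since the published sentences conflict with each other.

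**What to change.** The sponsor should reconcile four statements in Intervention description {11a} so that they can be met together:

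1. the minimum interval between doses;
2. the 1-hour permission, stating whether it covers late doses only;
3. the instruction on the next dose, stating what follows a late dose;
4. the two-capsule cap, stating whether the 24 hours is rolling or a calendar day.

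The same wording should then go into the subject instructions and the drug diary. Which rule gives way is a clinical decision for the sponsor, and no view on it is offered here.

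The cost is a wording amendment, with no extra visits or patients and no change to the analysis.

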#### Criteria for discontinuing or modifying allocated interventions {11b}

Subjects will be withdrawn from the study for the following:If the subject is unable or unwilling to take the study drug.Subjects planned for a NSRP but who did not receive a nerve-sparing procedure intraoperatively.Subjects who have experienced a seizure while taking the study medication.Subjects who take ED treatments within the 3-month period after surgery.Any subject with an eGFR less than 60 mL/min/1.73 m^2^ while on the study, if clinically indicated, will have a repeat serum BUN and creatinine within 2–3 days, and if eGFR is still less than 60 mL/min/1.73 m^2^, they will be promptly withdrawn from the study.In subjects who incidentally demonstrate a decrease in eGFR > 30 mL/min on study, but still maintain an eGFR ≥ 60 mL/min, we will obtain repeat BUN and creatinine within 2–3 days, and if eGFR based on repeat labs is < 60 mL/min, they will be promptly withdrawn from the study.Subjects with final surgical pathology showing pT3 disease, positive nodes, or positive surgical margins who require adjuvant treatment (such as androgen deprivation therapy or radiation) as adjuvant treatments can worsen ED and UI after NSRP.The Data Safety Monitoring Committee (DSMC) and/or principal investigator may withdraw any subject at increased risk using the best medical opinion based on reported AEs/SAEs.

